### Outcomes

The primary outcome is pain: self-evaluation of the maximum pain felt by the patient during the collection of an arterial blood sample on the Verbal Rating Scale (VRS: 0=no pain to 10=the worst imaginable pain) just before the beginning of the procedure and during the procedure (question asked during the 3 minutes after the procedure) [14,31,32].

The secondary outcomes are as follows:

Comfort: self-evaluation of patient comfort using a simple comfort VRS (0=no comfort to 10=the most comfort imaginable) just before the beginning of the procedure and 3 minutes after the procedure [33]Anxiety: self-evaluation of patient anxiety using a simple anxiety VRS (0=no anxiety to 10=the worst anxiety imaginable) just before the beginning of the procedure and 3 minutes after the procedure [34]Puncture failure: success of the first arterial puncture assessed by the accredited evaluator at the end of the procedure using the number of puncture points visible on the patient’s skin (possible response: 1 puncture visible, yes/no)Global satisfaction with the communication strategy used: evaluation by the patient at the end of the procedure using a numeric scale of 0-10 (0=extremely dissatisfied to 10=extremely satisfied)

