## Introduction

Pain, defined as a disagreeable sensory or emotional experience, is the most frequent symptom among patients admitted to the emergency department (ED). Karwowski-Soulié et al [1] estimate that this symptom can be observed in almost 80% of patients upon their arrival to the ED. Despite several international recommendations concerning pain management [2,3], pain in the context of an emergency often remains underestimated [4]. Medical procedures, such as venous or arterial blood collection, which are essential for diagnostic management and patient care, can also generate pain and a high level of stress for patients who are already weakened by their underlying condition [5]. This is known as “care-related pain” [6].

Arterial blood gas (ABG) sampling is necessary to assess the gravity of the patient’s condition and is a procedure conducted routinely in the ED. In a medium-size hospital (30,000 hospitalizations per year), approximately 1000 ABG tests are conducted annually [7]. However, arterial blood collection is generally associated with pain and patient anxiety [8].

To decrease the perception of pain linked to the collection of arterial blood, several methods have been studied, such as applying a topical anesthetic cream (eg, lidocaine, xylocaine) or administering a subcutaneous injection of lidocaine prior to the procedure [9]. Given that arterial blood collection is often performed in emergency situations and that the anesthetic cream must be applied at least 1 hour before sampling, this method is not adapted to emergency practices. In a previous study, a subcutaneous injection of lidocaine did not allow a significant reduction in pain during radial artery puncture [10]. Similarly, another study using ultrasound guidance for arterial blood sampling did not show any significant decrease in pain, the rate of immediate complications, or physician satisfaction [11].

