### Hypotheses

The principal hypothesis is as follows: Pain perceived during the collection of an arterial blood sample in the ED is lower when it is performed using positive therapeutic communication compared to neutral or nocebo communication.

The secondary hypotheses are as follows:

Discomfort perceived during the collection of an arterial blood sample in the ED is lower when the procedure is conducted using positive therapeutic communication compared to neutral or nocebo communication.Anxiety perceived during the collection of an arterial blood sample in the ED is lower when the procedure is conducted using positive therapeutic communication compared to neutral or nocebo communication.

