### Statistical Analysis

#### Sample Size Calculation

With a significance level of .05, a power of 0.9, a difference in pain on the VRS of 1.5 (generally accepted as clinically significant) with an expected SD of 2.5 [35], and an attrition of 20% on the basis of a group-independent *t* test (a specific case of linear mixed effects models [LMMs]), we must include 83 patients in each group to show the efficacy of the intervention on pain by applying the Bonferroni correction (ie, a total of 249 patients).

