## Discussion

### Summary

To the best of our knowledge, this is the first RCT that will investigate the effect of a positive communication over a routine procedure, such as ABG testing, in an emergency setting. Considering the KTHYPE study [15], a reduction in pain, anxiety, and discomfort can be expected when using positive communication.

Two of the ethical values in the medical field are beneficence and the objective to do no harm to the patient. However, although the nocebo effect of language is acknowledged today in specialties, such as anesthesiology, negative communication continues to be used daily in the ED, a particularly stressful setting with vulnerable patients. This makes it all the more important to study language tools in this environment, with the aim of standardizing and protocolizing caregivers' communication.

ABG testing is an investigation required in certain medical situations. The global experience of this procedure has often been described as disagreeable and can be improved [8]. The comfort and anxiety before and after sampling can be demonstrated. Today, no risk linked to the communication strategy has been documented, except for the usual inherent risks of arterial blood collection. The nocebo arm is nowadays commonly used in routine practice. If communication can lead to decreased pain, anxiety, and discomfort during this standard investigation, it will lead to changes in current practice. This method is easily used by even the most inexperienced doctors, and we hope that this will reduce their stress during the procedures.

Our study will also assess patient comfort and anxiety. These elements are of primary importance, as pain is frequent in emergencies and frequently underestimated (80% of patients [1]). The patient's anxiety and comfort level contribute to this pain, even if it has not been well documented. To interpret the results, we may compare the comfort and anxiety scores before and after the procedure. This will allow us to control for patients with chronic pathologies (eg, depression).

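### The primary pain rating is tied to the blood collection only in time, not to the puncture, and is modelled as change from an any-cause pain rating; pre-existing pain can dilute the arm difference and lower power

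*Protocol article*

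**What the plan says.** The Outcomes section makes pain the primary outcome: "self-evaluation of the maximum pain felt by the patient during the collection of an arterial blood sample", on a 0-10 verbal scale. It is rated just before the procedure and again, by a question put within 3 minutes afterwards, for the procedure itself. The principal hypothesis has the same scope: "Pain perceived during the collection of an arterial blood sample in the ED is lower" under positive communication than under the other two scripts.

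The Statistical Analysis Plan section fits linear mixed models to changes over time. It tests time, group and their interaction, with control for sociodemographic and health-status variables.

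On the population, the Introduction says that "this symptom can be observed in almost 80% of patients upon their arrival to the ED". The exclusion criteria under Population and Sample contain nothing on existing pain. The Introduction presents the problem as care-related pain, that is, pain generated by the procedure.

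The sample size rests on "a difference in pain on the VRS of 1.5 (generally accepted as clinically significant) with an expected SD of 2.5", a power of 0.9, a Bonferroni correction and 20% attrition.

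**The concern.** The scripts are meant to change how the puncture is felt, but the outcome definition fixes only a time window. A patient with abdominal pain of 8 and puncture pain of 3 who rates everything felt during the collection answers 8 whichever script was used. For a patient who answers that way, the score is the larger of two pains, and the script can move it only when the puncture is the worse of the two.

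The pre-procedure rating uses the same item before any needle has been used, so it measures any-cause pain. Modelling the two ratings as one outcome changing over time supports reading the second as any-cause pain too.

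At stake is the interpretation of a null result, which could not be told apart from a real effect on puncture pain masked by illness pain.

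**Working it through.** **1. The plan's own figure.** Inputs from Sample Size Calculation: difference 1.5, SD 2.5, power 0.9, overall level .05. Assumed: a two-sided test and a Bonferroni division by two (positive against neutral, positive against nocebo).

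n = 2 × (2.241 + 1.282)² × 2.5² / 1.5² = 68.95, so 69 per group. 69 × 1.2 = 82.8, so 83. The stated 83 per group is reproduced. With 20% lost, 83 × 0.8 = 66.4, so about 66 per arm are analysed.

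**2. What the planned contrast is.** With one rating before, one after and a patient random intercept, the group-by-time interaction is in essence a comparison of mean change scores.

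**3. Illustration.** The documents do not give the following inputs, so they are assumptions:
- puncture pain has mean 5.0 or 3.5, SD 2.5, limited to 0-10;
- illness pain is present in 80%, with mean 2 to 5 and SD 2.5, limited to 0-10, independent of puncture pain, unchanged by the script, and equal to the pre-procedure rating;
- the recorded score is the larger of the two pains.

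Power comes from the noncentral t distribution with 66 per arm and two-sided .025 (critical value 2.27). The noncentrality is difference / (SD × √(2/66)), where √(2/66) = 0.174.

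*Puncture-specific item:* the difference is 1.41 (below 1.5 because the scale has ends) and the SD 2.36. 1.41 / (2.36 × 0.174) = 3.43, so power is 0.88.

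*Larger of the two pains, 80% affected:*

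| Mean illness pain | Recorded difference | Post-score: SD, power | Change score: SD, power | Baseline-adjusted: residual SD, power |
|---|---|---|---|---|
| 2 | 1.15 | 2.18, 0.77 | 2.49, 0.65 | 2.07, 0.82 |
| 3 | 1.03 | 2.15, 0.69 | 2.45, 0.56 | 1.96, 0.78 |
| 4 | 0.90 | 2.16, 0.55 | 2.38, 0.46 | 1.83, 0.71 |
| 5 | 0.77 | 2.21, 0.40 | 2.29, 0.37 | 1.70, 0.63 |

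Example, last row, change score: 0.77 / (2.29 × 0.174) = 1.93, so power is 0.37. Powers are good to about 0.01.

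The share of the effect retained runs from 1.15 / 1.41 = 0.81 to 0.77 / 1.41 = 0.54.

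**4. Fewer affected.** With 40% affected and mean illness pain 5, the recorded difference is 1.09. Power is about 0.63 on the post-score, 0.53 on the change score and 0.77 with baseline adjustment.

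**5. Why adjustment and change differ.** Adjustment removes between-patient noise without forcing a slope of 1. In these simulations the fitted slope on the pre-procedure rating is about 0.33 to 0.48, so subtracting the whole rating adds noise. Neither method recovers a puncture rating that was never given, so the recorded difference is equally shrunken under both.

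**The case against.** The case on the other side is substantial.

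- **The question put to patients is not shown.** Outcomes is a definition in a condensed article. The case report form may already name the puncture. This stands, and the fix allows for it.
- **The context points to the procedure.** The recruitment script and Research Ethics Approval present the study as being about the patient's experience of this procedure. Some patients will therefore rate the puncture alone, and the larger-of-two rule is an assumed way of answering. This stands as a limit on size. It does not change what the endpoint says.
- **Hypothesis and outcome agree.** Both refer to pain during the collection, and the mechanism in the Introduction is not confined to the wrist, so a script might also ease illness pain. The illustration assumes that it does not.
- **The 80% is not a figure for this sample.** It is prevalence on arrival in all emergency patients, with no intensity. Indications for the test include dyspnea and metabolic disorders. Prevalence and severity in the trial are unknown.
- **The 1.5 and 2.5 are stated for the recorded score.** Applying them to puncture pain is a choice. If 1.5 is meant for an any-cause score, the effect on puncture pain would have to be larger to produce it.
- **Baseline pain is measured.** Used as a covariate it restores part of the power. Used as a change score, which is in essence what the plan describes, it does not in most of these settings.

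A reader might infer that the outcome simply records illness pain and hides the scripts' effect, or that the arms are compared unfairly. The documents support neither. Puncture pain still sets the score wherever it is the worse pain, and randomization balances illness pain.

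**Conclusion.** The concern holds as a weakness in how the primary endpoint is defined and modelled. As written, the rating is not attributed to the puncture, the pre-procedure rating can only be any-cause pain, and patients with existing pain are eligible. For patients who rate all pain, this shrinks a real effect on puncture pain and lowers power. It does not create a false difference.

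The size cannot be fixed from the documents. Under the stated assumptions with 80% affected, power falls from about 0.88 to between 0.65 and 0.37 on the planned change contrast, and to between 0.82 and 0.63 with baseline adjustment. The loss is smaller if fewer patients have pain, if their pain is mild, or if most understand the question as being about the puncture.

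**What to change.** 1. **Outcomes, and the case report form if it does not already say so:** define the post-procedure primary item as the maximum pain from the arterial puncture at the wrist during the collection.
2. **Pre-procedure rating:** keep it as a separate item, labelled current pain from any cause.
3. **Statistical Analysis Plan section:** compare the post-procedure rating between arms with the pre-procedure rating as a covariate. The two items would then measure different things, so they cannot be analysed as one outcome changing over time.
4. **If the wording changes during recruitment** (inclusion began in April 2023): apply it from the amendment date, include a wording-period term in the model, and add a sensitivity analysis in patients with low pre-procedure pain, with the cut-off set before the data are seen by arm.

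The cost is a few words in one question and a revised model statement. The planned 83 per group, visits and staff are unchanged. The downside of a mid-trial change is two wordings in one endpoint: the period term absorbs a shift in level, but the pooled effect would still average a possibly diluted effect with an undiluted one. If the form already names the puncture, only the article's definition and the model need correcting.

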### Statistical Analysis

#### Sample Size Calculation

With a significance level of .05, a power of 0.9, a difference in pain on the VRS of 1.5 (generally accepted as clinically significant) with an expected SD of 2.5 [35], and an attrition of 20% on the basis of a group-independent *t* test (a specific case of linear mixed effects models [LMMs]), we must include 83 patients in each group to show the efficacy of the intervention on pain by applying the Bonferroni correction (ie, a total of 249 patients).

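### The Bonferroni correction named for pain is valid, but Holm's procedure controls the same error rate with more power per contrast; a one-sentence improvement

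*Protocol article*

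**What the plan says.** All references are to the protocol article.

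- **Sample Size Calculation.** The calculation starts "With a significance level of .05", power 0.9, "a difference in pain on the VRS of 1.5" and "with an expected SD of 2.5", allows 20% attrition and is based on an independent-groups t test. It arrives at 83 per group (249 in total) "to show the efficacy of the intervention on pain by applying the Bonferroni correction". The number of comparisons and the sidedness are not given.
- **Hypotheses.** Pain "is lower when it is performed using positive therapeutic communication compared to neutral or nocebo communication". This implies two contrasts: positive against neutral, and positive against nocebo.
- **Statistical Analysis Plan (subsection of the article).** Significance is set at .05. Neither Bonferroni nor any other multiplicity procedure is named there.

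**The concern.** Bonferroni is the only multiplicity method the article names for pain. With two contrasts it tests each at .025 whatever the other one shows. Holm tests the smaller P value at .025 and, if that is significant, the other at .05. It controls the family-wise error under the same conditions as Bonferroni, and no data set leads Bonferroni to reject a hypothesis that Holm retains. For the tests themselves, Bonferroni is therefore dominated.

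At stake is the second contrast. A win over nocebo wording alone would leave open whether positive wording helps or negative wording harms, so the comparison with neutral wording carries much of the interpretation. If nocebo words raise pain, as the Nocebo Arm section expects, positive against neutral is probably the smaller difference and the one more easily missed. That ordering is an assumption, not a figure in the article.

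**Working it through.** **Inputs.** From Sample Size Calculation: α = .05 with Bonferroni, power 0.9, difference 1.5, SD 2.5, attrition 20%, 83 per group. From Hypotheses: two contrasts sharing the positive arm. Assumed, because not stated: two-sided tests.

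**Step 1: reproduce the stated 83.** With α/2 = .025 two-sided per contrast,

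n = 2 × SD² × (z₀.₉₈₇₅ + z₀.₉₀)² / difference² = 2 × 2.5² × (2.2414 + 1.2816)² / 1.5² = 68.95, so 69.

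69 × 1.2 = 82.8, so 83. This matches the article and supports two contrasts at two-sided .025. The match is not unique: a one-sided t test with three comparisons needs 66, and 66/0.8 = 82.5, also 83.

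**Step 2: patients left after the planned attrition.** 83 × 0.8 = 66.4, so 66 per arm.

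**Step 3: power per contrast at 66 per arm, both differences 1.5.** The standardised difference is (1.5/2.5) × √(66/2) = 3.447.

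- Bonferroni: Φ(3.447 − 2.241) = 0.886 (normal); 0.879 with the noncentral t.
- Holm: P(contrast 1 significant at .025) + P(contrast 1 significant only at .05 and contrast 2 significant at .025). The shared arm gives correlation 0.5. Normal result: 0.886 + 0.033 = 0.919.

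**Step 4: simulation**, shared positive arm, pairwise t tests, 1,000,000 trials per setting, both differences 1.5:

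| Analysable per arm | Quantity | Bonferroni | Holm |
|---|---|---|---|
| 66 | one given contrast | 0.880 | 0.915 |
| 66 | both contrasts | 0.802 | 0.872 |
| 66 | at least one | 0.958 | 0.958 |
| 83 | one given contrast | 0.945 | 0.965 |
| 83 | both contrasts | 0.903 | 0.944 |
| 83 | at least one | 0.986 | 0.986 |

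With the variance pooled over the three arms the figures are marginally higher. At 66 they are 0.882 against 0.917 per contrast and 0.805 against 0.874 for both. At 83 they are 0.946 against 0.966 and 0.905 against 0.945. The row for at least one contrast is identical by construction, because Holm's first step is the Bonferroni test.

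**Step 5: unequal differences**, 66 per arm, first contrast 1.5, pairwise t tests:

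| Second difference | First contrast: Bonferroni → Holm | Second contrast: Bonferroni → Holm |
|---|---|---|
| 0 | 0.880 → 0.882 | 0.025 → 0.045 (error rate) |
| 1.0 | 0.880 → 0.891 | 0.514 → 0.614 |
| 2.0 | 0.879 → 0.926 | 0.990 → 0.993 |

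**Step 6: error control**, pooled variance. With both contrasts null the family-wise error is 0.046 for both methods. With one null and the other very large (3.0), Holm's error on the null contrast is 0.050. Control at .05 holds.

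**The case against.** **The article does not fix the rule being criticised.** A reader might infer that the plan prescribes two contrasts, single-step, each tested at .025. It does not: Bonferroni appears only in the sample size sentence, and the analysis section names no procedure. Sizing each contrast at .025 is also a usual conservative way to size a trial that will be analysed with Holm. This stands. The point is therefore about the one correction the article names, and the article's text is compatible with the improvement. A separate statistical analysis plan, not shown, may already settle the matter.

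**Bonferroni is not an error.** This also stands; the gain is one of efficiency.

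**Needing both contrasts is a co-primary argument.** If success required both, no split of α would be needed. Testing each at .05 gives 0.880 for both at 66 per arm, slightly above Holm's 0.875 in the same simulation. If either contrast suffices, the two methods have the same power. Holm gains only when each contrast is to be claimed individually. This stands, and the fix should state which claim is intended.

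**The 0.88 baseline is low for another reason.** A reader might blame Bonferroni for power below the planned 0.90. At the 69 analysable per arm that the calculation aimed for, Bonferroni gives about 0.895. The drop to 0.88 comes from adding attrition as × 1.2 where 69/0.8 gives 87. Holm does not correct that; it is a separate point. The article also expects few missing values, and with all 83 analysable Holm adds only 0.02 per contrast.

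**It is not free.** Two 97.5% intervals remain the simple simultaneous intervals, and one can include zero when Holm rejects. This is a real but modest reporting cost.

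**Conclusion.** The point holds as a cheap improvement to a valid choice. Holm controls the same family-wise error as Bonferroni and is never less powerful. Under the article's own assumptions (both differences 1.5, SD 2.5), it raises power per contrast from about 0.88 to 0.92 and power for both from about 0.80 to 0.87 with 66 analysable per arm. With 83 analysable, the gains are about 0.02 and 0.04. It adds nothing to the chance of winning at least one contrast, and almost nothing for a real contrast when the other is null.

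The conclusion rests on two contrasts and two-sided tests, which are inferred from the Hypotheses section and the reproduced 83. The calculations use t tests and ignore clustering by physician and covariate adjustment, as the article's own calculation does. The documents do not support a stronger reading, such as that the plan is wrong to use Bonferroni or that the trial is undersized because of it.

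**What to change.** State once, in Sample Size Calculation and again in the Statistical Analysis Plan subsection, before the data are analysed by arm:

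> The two primary pain contrasts (positive–neutral and positive–nocebo) are tested with the Holm procedure at a family-wise two-sided level of .05, and each contrast is claimed individually. Simultaneous 97.5% confidence intervals are reported for both.

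This also settles the number of contrasts, the sidedness, and how the .05 in the analysis section relates to the correction. The sponsor should confirm that these match its intention, since the sentence fixes more than the name of the correction.

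Cost: one sentence, with no extra patients or data. The intervals stay at Bonferroni width, so the report should explain that an interval may occasionally include zero when the Holm test rejects. The attrition arithmetic has to be dealt with separately.

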#### Statistical Analysis Plan

First, descriptive statistics (frequencies and percentages for categorical data; means, SDs, medians, and IQRs for quantitative data) will be run for each measure of time for each group and the overall study sample. In addition, an analysis of nonresponses and patient dropouts will be conducted. Second, bivariate associations will be calculated to compare the groups at baseline (Pearson chi-square test, Fisher exact test, *t* test, and the Mann-Whitney test according to the distribution of variables). Third, to test the impact of the intervention on the different outcomes (hypotheses 1, 2, and 3), LMMs with patients, groups and physicians as a random effect will be performed to analyze changes over time. The participation of approximately 25 physicians is foreseen in this study. The models will be tested on all available data.

The effects of time, groups, and their interaction will be tested by controlling for sociodemographic characteristics and variables linked to health status. An intention-to-treat (ITT) analysis, per protocol (PP) and based on the analysis of communications (ie, the respect of the quality of the defined communication according to the protocol; see the next section), will be conducted. The Pearson chi-square test comparing the allocation defined in the protocol and the allocation following the analysis of communications will be performed. If necessary, a generalized LMM will also be used to explore the differences between the available measured variables (physicians having performed the ABG procedure, pain, etc). Statistical analysis will be performed on available data, and no imputation of missing data will be conducted. Given that our study will be conducted on a 1-to-1 basis with a member of the research team and on the basis of previous experience, we expect that the number of missing values will be low. Statistical analyses will be performed using the R (R Core Team and the R Foundation for Statistical Computing) and STATA version 12 (StataCorp); the level of significance will be set at *P*=.05.

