## Methods

### Study Design

This study will be a single-center, double-blind randomized controlled trial (RCT) with 3 parallel arms. To minimize bias during the intervention itself, the communication strategy will be clearly defined beforehand. The evaluator (any person [physician/student/other] assessing patient outcomes before and after arterial blood collection but playing no role in patient management in the ED or in the conducting of the procedure and without any knowledge of the study arm assigned to the patient at randomization) will be blinded to the strategy used.

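### The mixed model for the primary analysis gives the randomised group two incompatible roles: it is listed as a random effect and then tested as a fixed effect

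*Protocol article*

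**What the plan says.** The Study Design section describes a "single-center, double-blind randomized controlled trial (RCT) with 3 parallel arms". The arms are three named communication styles chosen by the investigators. The principal hypothesis is that pain "is lower when it is performed using positive therapeutic communication compared to neutral or nocebo communication"; the two secondary hypotheses make the same comparison for discomfort and anxiety.

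The Statistical Analysis Plan section names one class of model for all three hypotheses: "LMMs with patients, groups and physicians as a random effect will be performed to analyze changes over time". On the physician term it adds: "The participation of approximately 25 physicians is foreseen in this study". The following paragraph reads: "The effects of time, groups, and their interaction will be tested by controlling for sociodemographic characteristics and variables linked to health status".

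The Sample Size Calculation section rests on an independent-groups t test, described there as a special case of a linear mixed model, with a Bonferroni correction and 83 patients per group.

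**The concern.** A random effect suits a factor whose levels stand for a wider population and whose individual differences are not the question. Patients fit that description, and so do about 25 physicians. The three arms do not: they are the only levels of interest, and the differences between them are what the trial is for.

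The model sentence puts group with patients and physicians, while the next paragraph treats it as an effect to be tested. An analyst who follows the first statement obtains no arm contrast. One who follows both enters group twice, which is redundant and can damage some of the inference. One who follows only the second obtains the right model by setting the first aside. These choices can lead to different estimates and standard errors for hypotheses 1 to 3, and the text should not leave the choice open.

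**Working it through.** **1. The role of group in each section**

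| Section | Role of group |
|---|---|
| Hypotheses | Fixed: positive against neutral or nocebo |
| Sample Size Calculation | Fixed: difference between two group means |
| Statistical Analysis Plan, model sentence | Random, with patients and physicians |
| Statistical Analysis Plan, next paragraph | Fixed: tested with time and the interaction |

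Three of the four statements need a fixed effect, and one contradicts them.

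**2. What the sample size assumes**

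The inputs are "With a significance level of .05, a power of 0.9, a difference in pain on the VRS of 1.5" and "with an expected SD of 2.5 [35], and an attrition of 20" percent. A two-sided test is assumed, because sidedness is not stated. The number of Bonferroni comparisons is not stated either, so it was varied.

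- n = 2(z₁₋α/₂ + z₁₋β)²σ²/δ². With two comparisons α = 0.05/2 = 0.025, so n = 2 × (2.241 + 1.282)² × 6.25/2.25 = 68.95, rounded up to 69.
- 69 × 1.2 = 82.8, rounded up to 83 per group; 3 × 83 = 249. This reproduces the stated figure.
- With the same formula and inflation, one comparison gives 59, then 71; three give 76, then 92. Neither matches.

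The trial is therefore sized for two fixed pairwise contrasts.

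**3. Group random only (illustration)**

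Take 83 × 0.8 = 66 completers per arm, SD 2.5, one post-procedure score, and the positive arm 1.5 points below two equal arms. The model returns one between-group variance τ² and predicted group means shrunk by the factor

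w = τ²/(τ² + σ²/n).

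- The arm means deviate from their average by −1, 0.5 and 0.5, so their variance is 1.5/2 = 0.75.
- σ²/n = 6.25/66 = 0.095.
- At these values w = 0.75/0.845 = 0.89, which predicts 1.5 × 0.89 = 1.33.
- In 20,000 simulated trials, with τ² estimated each time, the mean of w was 0.85 and the mean predicted difference 1.31. The ordinary fixed-effect difference averaged 1.50.
- With no true difference, τ² was estimated as zero in about 64% of runs.

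**4. Group both fixed and random**

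Let each arm have a random intercept u with variance τ². The fixed arm term already fits the arm means exactly, so the data carry no information on τ² and the restricted likelihood is flat in it. Its effect depends on the contrast.

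- *Arm difference at one time.* The difference u₁ − u₂ remains, so SE² = 2σ²/n + 2τ². Leaving physicians out, 2σ²/n = 12.5/66 = 0.189.

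| τ² | SE of arm difference |
|---|---|
| 0 | √0.189 = 0.435 |
| 0.1 | √0.389 = 0.62 |
| 1 | √2.189 = 1.48 |
| 5 | √10.189 = 3.19 |

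- *Group-by-time contrast.* Each patient's change is (later score + u) − (baseline score + u), so u cancels and τ² drops out.

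A generalised least squares check with two times, patient intercepts and 25 physician intercepts agreed. The group main-effect standard error rose from 0.43 at τ² = 0 to 3.19 at τ² = 5, while the group-by-time standard error stayed at 0.435. The variance components are assumed, with a total close to an SD of 2.5.

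**The case against.** The strongest reply is that the intention can be recovered. The next paragraph promises tests of time, group and interaction with covariate adjustment, and the hypotheses and sample size point the same way. On this view, one misplaced word in a list contradicts an otherwise consistent plan. That largely stands, and it rules out three stronger readings that a reader might infer.

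- *That the plan contains no test of the arm differences.* It does promise one; the fault is that the model sentence conflicts with that promise.
- *That the planned analysis would understate the effect as 1.31 instead of 1.5.* That figure belongs to a single-score layout with group random only. The plan describes a model with time and interaction, and nowhere says that the effect will be reported as a shrunken prediction.
- *That entering group twice invalidates every standard error.* It does not. The plan analyses changes over time, and the group-by-time contrasts are untouched by a random group intercept.

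It is also fair to say that an article may leave the full model formula and the list of contrasts to a separate analysis plan. Their absence is not held against the document. The random-effect phrase is different: it is a positive statement about the model, and it is wrong.

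A charitable reading is that the arm effect was meant to vary randomly between physicians, since each physician works in all three arms. That would be legitimate, but the sentence does not say it.

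**Conclusion.** Wrong as written. The Statistical Analysis Plan section contradicts itself on the role of the randomised group in the only class of model named for hypotheses 1 to 3, and its random-effect statement also conflicts with the hypotheses and the sizing.

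The size of the consequence depends on how the text is implemented. With group random only, there is no arm contrast, and the predicted differences are shrunk by roughly 13% in the illustration (1.31 against 1.50). With group entered both ways, the group main-effect standard error depends on a variance that the data cannot estimate; it rises from 0.43 to 3.19 if that variance is 5, and the group-by-time contrasts are unaffected. With group fixed only, there is no harm.

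These figures assume 66 completers per arm, SD 2.5 and, for the second case, chosen variance components. They show why the wording should be settled, and are not an estimate of bias in the analysis that the sponsor probably intends. The stated sample size is not altered by this point.

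**What to change.** Remove groups from the list of random effects and replace the model sentence with one such as:

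> Linear mixed models will include arm (three levels), time and arm-by-time as fixed effects, with random intercepts for patient and physician; the treatment effects are the fixed contrasts positive minus neutral and positive minus nocebo, with Bonferroni correction.

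Two comparisons, each at 0.025 two-sided, match the sample size calculation. If an arm effect that varies by physician was intended, it should be stated as a random arm slope within physician, alongside the fixed arm effect.

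The cost is one sentence. It needs no new data and no change to the number of patients.
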